### 2.6. Outcome Measures

Participants will undergo evaluations at three time points: baseline (T0), post-intervention (T1), and follow-up (T2) (refer to Figure 1, ‘Study Period’).

#### 2.6.1. Primary Outcome Measure

The primary outcome will be the assessment of change (T0-T1-T2) in static and dynamic balance, measured using the Mini-Balance Evaluation System Test (Mini-BESTest) [50]. The Mini-BESTest is designed to assess the underlying systems of postural control that contribute to poor functional balance. It includes 27 tasks (36 items in total) that evaluate biomechanical constraints, stability limits/verticality, anticipatory responses, postural responses, sensory orientation, and gait stability. Each item is scored on an ordinal scale from 0 to 3, with 3 indicating the best performance and 0 the worst. The total score is presented as a percentage, with higher scores reflecting better performance.

Items 7 and 8 (upright standing with eyes open on a rigid surface and with eyes close on foam, respectively) and Item 11 (walking with right/left head turns) of the Mini-BESTest will be administered in their sensorized version using three inertial measurement units (IMU) (Xsens MTw, Movella, NV, USA) attached on the lower back (L5 level) and above both lateral malleoli. Accelerometric and gyroscopic signals from the IMUs will be used to compute a set of digital metrics descriptive of gait spatio-temporal parameters (e.g., cadence, stance phase duration), stride regularity, gait symmetry, and dynamic stability for Item 11, and a set of balance indexes (i.e., sway amplitude and complexity) for the posturographic tasks involved in Items 7 and 8 [51]. See Figure 4 for a representative output of a sensorized version of the Mini-BESTest.

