## Abstract

Parkinson’s disease (PD) and multiple sclerosis (MS) are two chronic neurological diseases (CNDs) that have a high demand for early and continuous rehabilitation. However, accessing professional care remains a challenge, making it a key priority to identify sustainable solutions for ensuring early rehabilitation availability. **Objective**: The FIT4TeleNEURO pragmatic trial proposes to investigate, in real-life care settings, the superiority in terms of the effectiveness of early rehabilitation intervention with harmonized, mix-model telerehabilitation (TR) protocols (TR single approach, task-oriented—TRsA; TR combined approach, task-oriented and impairment-oriented—TRcA) compared to conventional management (control treatment, CeT) in people with PD and MS. **Design, and Methods**: This multicenter, randomized, three-treatment arm pragmatic trial will involve 300 patients with CNDs (PD, N = 150; MS, N = 150). Each participant will be randomized (1:1:1) to the experimental groups (20 sessions of TRsA or TRcA according to a mix-model—3 asynchronous + 1 synchronous session/week) or the control group (20 sessions of CeT). Primary and secondary outcome measures will be obtained at the baseline (T0), post-intervention (T1, 5 weeks after baseline), and follow-up (T2, 3 months after the end of the treatment). A multidimensional evaluation (cognitive, motor, and quality of life domains) will be conducted at each time point of assessment (T0; T1; T2). The primary outcome measures will be the assessment of change (T0 vs. T1 vs. T2) in static and dynamic balance, measured using the Mini-Balance Evaluation Systems Test. Usability and acceptability assessment will be also investigated. **Expected Results**: Implementing TR protocols will enable a more targeted and efficient response to the growing demand for rehabilitation in the early stages of CNDs. Both the TRsA and TRcA approaches are expected to be more effective than CeT, with the combined approach likely providing greater benefits in secondary outcome measures. Finally, the acceptability of the asynchronous modality could open the door to scalable solutions, such as digital therapeutics.

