### 2.2. Sample Size

The sample size was determined a priori using G*Power 3 software, based on previously published preliminary data [30] related to the study’s primary outcome, the Mini-Best test. Assuming a minimal clinically important difference (MCID) of 3 points (ds group 1 = 5.75, ds_group 2 = 5.98), a statistical power of 80% (type I error rate of 0.05), and an allocation ratio of 1:1:1, 48 subjects per group are required. These groups include TR with single approach (TRsA) and the control group. A third group (TR with combined approach, TRcA) of 48 subjects will be recruited to assess whether a neuromotor rehabilitation program combining two approaches (task-oriented and impairment-oriented) is superior to the control group and differs from the TRsA group in secondary outcomes. The study will recruit 144 patients with Parkinson’s disease and 144 patients with multiple sclerosis. To account for a potential 5% drop-out rate per pathology group, a total of 300 subjects will be enrolled.

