### 2.8. Statistical Analysis

Descriptive statistics will be employed to characterize the sample, with mean and standard deviation (SD) reported for normally distributed variables, and median and interquartile range (IQR) for non-normally distributed variables.

Data analysis will follow the modified intention-to-treat (mITT) principle [70], ensuring that all participants with available baseline data are included in the analysis. Missing data will be addressed using multiple imputation techniques to minimize bias and enhance the robustness of findings. However, we will also conduct a complete records analysis as a comparison. To test the effect of the treatment on the outcome measures, generalized linear mixed models (GLMMs) [71] will be employed. The model will evaluate changes over time (T0, T1, T2) and differences between groups (TRsA, TRcA, CeT), with outcome scores serving as dependent variables. Independent variables (fixed factors) will include time, group, and the interaction term (time × group) to capture both main effects and interaction effects. 

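### The primary outcome, the sample size and the model do not describe one primary test, so the stated 0.05 type I error is not secured

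*Protocol article*

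**What the plan says.** - **Visits.** Section 2.6.1: "The primary outcome will be the assessment of change (T0-T1-T2) in static and dynamic balance", measured by the Mini-BESTest. The Abstract gives the same three time points. Post-treatment (T1) and the 12-week follow-up (T2) have equal rank.
- **Arms.** The Abstract sets out to show superiority of the telerehabilitation protocols over CeT and adds: "Both the TRsA and TRcA approaches are expected to be more effective than CeT". Section 2.2 recruits the third arm to learn whether a programme "combining two approaches (task-oriented and impairment-oriented) is superior to the control group and differs from the TRsA group in secondary outcomes".
- **Error budget.** Section 2.2 specifies "a statistical power of 80% (type I error rate of 0.05") and concludes with "an allocation ratio of 1:1:1, 48 subjects per group are required". It then says which comparison this is: "These groups include TR with single approach (TRsA) and the control group". TRcA is added at the same size, with no share of the 0.05.
- **Diseases.** Section 2.2 repeats the 3 × 48 calculation in PD and in MS (144 each). The Introduction lists the differential impact on the two cohorts as a secondary objective.
- **Model.** Section 2.8: "The model will evaluate changes over time (T0, T1, T2) and differences between groups (TRsA, TRcA, CeT"). The fixed factors listed are time, group and time × group. There is no disease term.

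**The concern.** A sample size, a primary outcome and a primary model should all point to the same test. Here the sizing is one two-group contrast at an unnamed time within one disease. The outcome covers two post-baseline visits and two active arms. The model is a three-group, three-time interaction in a sample that pools the diseases.

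As the article stands, a difference from CeT at T1 or at T2, for either arm, could be presented as the primary result. The 0.05 was budgeted for only one of those four routes, and the 80% power belongs to neither the interaction nor the set of four. The choice has to be settled before unblinded results are seen, because a visit or arm chosen afterwards would carry no credible error rate.

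**Working it through.** **1. Reproduce the 48 per group.** Inputs from Section 2.2: "Assuming a minimal clinically important difference (MCID) of 3 points (ds group 1 = 5.75, ds_group 2 = 5.98"), 80% power, type I error 0.05.

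- Pooled SD = √[(5.75² + 5.98²)/2] = 5.866, so d = 3/5.866 = 0.511.
- n per group = 2(z_α + z_β)²/d².
- One-sided 0.05: 2(1.645 + 0.842)²/0.511² gives 48. A noncentral-t check also gives 48, with power 80.0%.
- Two-sided 0.05: 2(1.960 + 0.842)²/0.511² gives 61. Power at 48 is 70.7% (normal) or 69.8% (t).

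The stated figure reproduces exactly, but only as one comparison at one-sided 0.05. The article does not state the sidedness.

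**2. The interaction.** Three groups and three times give (3 − 1)(3 − 1) = 4 degrees of freedom. This test can reject because TRsA and TRcA differ from each other, or because of one visit alone. Rejection does not show that either arm beats CeT. The sized contrast has 1 degree of freedom.

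**3. Chance of at least one false positive if arm-by-visit contrasts are tested unadjusted at 0.05.** With equal allocation, each contrast with CeT has variance 2σ²/n. Two contrasts sharing CeT have covariance σ²/n, so their correlation is 0.5. The correlation ρ between the T1 and T2 contrasts is not in the article and is taken from 0 to 0.9. The rates come from 2,000,000 multivariate normal draws under no effect.

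| Contrasts with CeT | One-sided | Two-sided |
|---|---|---|
| Two arms, one visit | 8.8% | 9.1% |
| One arm, two visits (ρ 0.9 to 0) | 6.8–9.8% | 7.0–9.8% |
| Two arms, two visits, ρ = 0.9 | 11.8% | 12.6% |
| Two arms, two visits, ρ = 0.7 | 13.8% | 14.9% |
| Two arms, two visits, ρ = 0.5 | 15.1% | 16.2% |
| Two arms, two visits, ρ = 0 | 16.8% | 17.4% |

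For scale, four independent tests would give 1 − 0.95⁴ = 18.5%.

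**4. Power for the possible populations** (same difference and SD throughout).

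- Per disease, 48 per group: 80% at one-sided 0.05, about 70% at two-sided 0.05, and 59–60% at two-sided 0.025.
- Pooled, 2 × 48 = 96 per group: about 97% at one-sided 0.05 and 94% at two-sided 0.05. This assumes that the effect and SD are the same in PD and MS.

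**The case against.** **The analysis plan may settle it.** A statistical analysis plan is not shown and may fix contrasts, adjustment and order. This stands as far as it goes: a reader might infer that the 5% is breached in fact, and the documents do not show that. The inflated rates arise only if the contrasts are tested unadjusted. But the visit of the primary endpoint belongs in the protocol, and the article itself states an outcome, a sizing and a model that do not match. A later plan that chose among them would still leave these sections to be reconciled.

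**One omnibus interaction test holds 0.05.** This is true under the global null of no difference in change anywhere. The article does not name it as the deciding test, it does not support a claim about either arm, and the stated power does not apply to it.

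**TRcA may be only a supporting arm.** In Section 2.2 the words on secondary outcomes could be read as covering both TRcA comparisons. The Abstract points the other way: it expects both arms to beat CeT and ties only the extra benefit of the combined approach to secondary outcomes. Even with TRcA set aside, one arm at two visits gives about 7–10%.

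**The stronger reading by disease.** A reader might infer from the per-disease sizing that PD and MS are two separate primary claims, making eight contrasts and a rate of about 22–32%. The documents do not support this. The disease difference is a secondary objective and the model has no disease term. What does stand is the conflict between per-disease sizing and a pooled model.

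**Conclusion.** The point holds as a failure to fix one primary test. The primary outcome names no visit, superiority is sought for two arms, and the single 0.05 is budgeted for one contrast that the named interaction does not test. The stated error rate is not secured. It would be about 9% for both arms at one visit and about 12–17% over both visits. These figures assume unadjusted testing at 0.05, a shared control with equal allocation, and a T1–T2 correlation between 0 and 0.9. Whether the primary population is pooled or per disease is a separate inconsistency between Sections 2.2 and 2.8, and it too must be resolved before the power statement has a definite meaning.

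**What to change.** In Sections 2.2, 2.6.1 and 2.8, before any unblinded result is seen:

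1. Name one primary visit, for example T1 (end of treatment), with T2 secondary for durability. The choice is the sponsor's, since the article favours neither.
2. Make the group difference in Mini-BESTest at that visit, adjusted for T0, the deciding contrast. The omnibus interaction should not decide success.
3. Test TRsA v CeT first, as the contrast that was sized, and TRcA v CeT only if it succeeds. Keep TRcA v TRsA among the secondary comparisons.
4. State whether the primary population is pooled or per disease, and align the model with the sizing. If per disease, there are two options:
   - Label each claim as disease-specific and run the sequence at 0.05 in each. This accepts 1 − 0.95² = 9.75% across the two diseases.
   - Use Holm across the diseases, starting at 0.025. The plan must then say how a released share of the error is passed on, because the same share cannot go both to TRcA and to the other disease.
5. State the sidedness and the resulting power, using the figures in step 4 of the working.

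**Cost.** The change takes a few sentences. The fixed order itself takes no power from TRsA v CeT, but TRcA cannot be claimed if TRsA fails. Stating two-sided tests within each disease does change the power claim: about 70% in place of 80%, and about 60% at the first Holm step. Holding 80% at two-sided 0.05 within a disease would need 61 per group.

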#### 2.6.2. Secondary Outcome Measures

Secondary outcomes will include the changes in cognitive and motor measures assessed at each evaluation time point (T0, T1, and T2).

Changes in dynamic and static balance will be measured by the Fullerton Advanced Balance Scale (FAB) [52,53], which evaluates dynamic and static balance under different situations. The FAB scale consists of 10 items that assess different aspects of balance, such as standing with eyes closed, reaching forward, turning, stepping, and standing on one leg. Each activity is scored on a 5-point scale ranging from 0 to 4, with higher scores indicating better performance. The total score can range from 0 to 40, and a score of 25 or lower suggests balance disturbances.

The modified Dynamic Gait Index (mDGI) [54] will also be used to assess changes in dynamic balance. The mDGI evaluates the ability to adapt gait to complex tasks using 8 tasks and 3 performance facets: gait pattern score (0–3), level of assistance (0–2), and time level score (0–3). The total score for each task (ranging from 0 to 8) is calculated by summing the scores from the 3 performance facets. Higher scores reflect better performance.

Changes in the perceived stability during activities of daily living will be measured by the Activities Balance Confidence scale (ABC) [55,56], while changes in the perceived fatigue in daily life will be measured by the Fatigue Severity Scale (FSS) [57,58].

The ABC is a 16-item questionnaire designed to assess an individual’s confidence in performing activities without the fear of falling or feeling unsteady. Each item is scored on a scale from 0 to 100, with higher scores reflecting greater perceived stability.

The FSS questionnaire includes nine items that assess the severity of fatigue symptoms in daily life activities. Each item is scored on a scale from 1 to 7, with higher scores reflecting greater perceived fatigue.

Changes in functional lower limb strength will be assessed using the Five Times Sit-to-Stand Test (5xSTS) [59,60]. The 5xSTS assesses functional lower limb strength, transitional movements, balance, and fall risk. The scoring is based on the time it takes for a patient to transition from a seated to a standing position and back to sitting five times. A shorter time to complete the test indicates a better outcome.

The Timed 25 Foot Walk (T25FW) [61] will be used to assess changes in mobility and leg function performance. The patient is instructed to walk 25 feet as quickly as possible, starting from one end of a marked 25-foot course. The timing begins when the instruction is given and stops when the patient reaches the 25-foot mark. The task is then repeated, with the patient walking back the same distance. The final score is the average time of the two completed trials.

Change in aerobic capacity and endurance will be measured with the 6-Minute Walk Test (6MWT). The 6MWT evaluates aerobic capacity and endurance. The distance covered in 6 min serves as the outcome measure to compare changes in performance capacity. An increase in the distance walked indicates an improvement in basic mobility. The 6MWT could be administered in its sensorized version using three IMUs on the lower trunk and ankles, as detailed by Carpinella and colleagues [62] (optional evaluation).

The general cognitive functioning will be evaluated with the Montreal Cognitive Assessment test (MoCA) [48]. The MoCA test is a highly sensitive screening battery for the detection of cognitive decline. The total score ranges from 0 to 30, and higher scores are indicative of better global cognitive performance.

The Trail Making Test (TMT) [63] and the Symbol Digit Modalities Test (SDMT) [64] will be administered to assess visuo-perceptual and attentional abilities.

The TMT is a neuropsychological test that involves visual scanning (TMT-A) and dual-task (TMT-B). It is scored by how long it takes to complete each part of the test. Longer execution times suggest lower performance.

The SDMT is a commonly used test to assess psychomotor speed. This paper-and-pencil assessment involves a substitution task using a coding key with nine different abstract symbols, each paired with a numeral. Below the key, a series of these symbols is presented, and the participant is asked to write down the corresponding number for each symbol. The score is based on the number of correct substitutions made within 90 s, with higher scores indicating better performance.

Change in the perceived level of disability will be measured by the World Health Organization Disability Assessment Schedule 2.0 (WHODAS 2.0) [65]. The WHODAS 2.0 evaluates functioning and disability levels across six domains: cognition, mobility, self-care, getting along, life activities, and participation in community activities, in line with the International Classification of Functioning, Disability, and Health (ICF). The summary scores for the WHODAS 2.0 are calculated in three steps: first, by summing the item scores within each domain; second, by summing the scores across all six domains; and third, by converting the total score into a metric ranging from 0 to 100, where 0 indicates no disability and 100 indicates full disability.

Finally, change in depressive symptoms will be evaluated with the Beck Depression Inventory (BDI-II) [66]. The BDI-II is a 21-item questionnaire, with each item rated on a 4-point scale (0–3). The score is obtained by summing the ratings for each item, with a range of 0 to 63. Higher scores indicate a greater deviation from a normal mood tone.

#### 2.6.3. Other Outcome Measures

The perceived usability of a technological system or device will be evaluated with the System Usability Scale (SUS) [67], a 10-item questionnaire. Each item is scored on a Likert scale from 0 to 5, with the total score ranging from 0 to 100. Higher scores indicate better perceived usability.

The Technology Acceptance Model-3 (TAM3) questionnaires [68] will be adopted to evaluate the user acceptance of technology across 16 domains. Scoring is based on a Likert scale (from 1 = Strongly Disagree to 7 = Strongly Agree) or a 10-point Guttman scale. Higher scores are indicative of higher acceptance of technology.

Finally, the Barthel Index [69] will be used to measure a person’s ability to perform basic activities of daily living (ADL) independently. It evaluates 10 functions, such as feeding, bathing, dressing, toileting, mobility, and stair climbing. Each activity is scored based on the level of assistance required, with a total score ranging from 0 (completely dependent) to 100 (completely independent).

### 2.7. Data Collection

The study includes the collection of clinical characteristics (e.g., the baseline motor function levels and the “ON” state during the multidimensional assessment through the Movement Disorder Society—Unified Parkinson’s Disease Rating Scale—MDS-UPDRS, Part III, [45]; the EDSS level, [47]; the age of onset, and the disease duration) and demographic information (e.g., age, education) at baseline (T0). Additionally, participants’ familiarity with and competence in using technological devices will be evaluated through an ad hoc questionnaire on technological expertise.

Data will be gathered at pre-intervention (T0), post-intervention (T1), and follow-up (T2) assessments from primary and secondary outcome measures (see the “Outcome” section of this document), with evaluations conducted by an assessor blinded to the assigned treatment. Post-intervention (T1), data on the usability, acceptability, and safety of the technological solutions will also be collected (see the “Other outcome measures” section). Safety concerns, including adverse events related to the intervention during the study, will be assessed using a clinical questionnaire.

For the TRsA and TRcA groups, data on adherence to the rehabilitation program and performance levels during exercises will be automatically recorded through the TR platform of the digital devices. In contrast, the CeT group will track adherence using a booklet.

All data collected from the three evaluation time points, along with treatment data from the digital platforms, will be entered into the REDCap database.

### 2.8. Statistical Analysis

Descriptive statistics will be employed to characterize the sample, with mean and standard deviation (SD) reported for normally distributed variables, and median and interquartile range (IQR) for non-normally distributed variables.

Data analysis will follow the modified intention-to-treat (mITT) principle [70], ensuring that all participants with available baseline data are included in the analysis. Missing data will be addressed using multiple imputation techniques to minimize bias and enhance the robustness of findings. However, we will also conduct a complete records analysis as a comparison. To test the effect of the treatment on the outcome measures, generalized linear mixed models (GLMMs) [71] will be employed. The model will evaluate changes over time (T0, T1, T2) and differences between groups (TRsA, TRcA, CeT), with outcome scores serving as dependent variables. Independent variables (fixed factors) will include time, group, and the interaction term (time × group) to capture both main effects and interaction effects. 

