### 2.1. Trial Design and Setting

This pragmatic study is designed as a single-blinded, randomized, three-treatment-arm (1:1:1) study involving chronic outpatients from neurorehabilitation units of 10 FIT4TeleNEURO Centers: (1) IRCCS Fondazione Don Carlo Gnocchi ONLUS, Milano (MI); (2) IRCCS Fondazione Don Carlo Gnocchi ONLUS, Roma (RO); (3) IRCCS Fondazione Mondino, Pavia (PV); (4) IRCCS Istituti Clinici Scientifici Maugeri, Bari (BA); (5) IRCCS Istituti Clinici Scientifici Maugeri, Milano (MI); (6) IRCCS Istituti Clinici Scientifici Maugeri, Pavia (PV); (7) IRCCS Istituti Clinici Scientifici Maugeri, Montescano (PV); (8) IRCCS Istituti Clinici Scientifici Maugeri, Telese (BN); (9) Università di Modena e Reggio Emilia, Modena (MO); and (10) Ospedale Valduce, Centro di Riabilitazione “Villa Beretta”, Como (CO).

Following enrollment and the baseline assessment, each participant will be randomly assigned into one of the following three groups, with an allocation ratio of 1:1:1: (1) telerehabilitation single approach (TRsA, experimental group); (2) telerehabilitation combined approach (TRcA, experimental group); or (3) conventional educational treatment (CeT, placebo comparator).

Randomization will be stratified based on both the clinical center and the clinical conditions (MS, PD). Primary and secondary outcome measures will be collected at baseline (T0), post-intervention (T1, 5 weeks after baseline), and at follow-up (T2, 12 weeks after treatment completion). The trial work plan is shown in Figure 2.

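### The model in Section 2.8 leaves arm means at T0 free, so its treatment contrast is a valid but less precise change-score comparison; adjusting for baseline is a free improvement.

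*Protocol article*

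**What the plan says.** Section 2.8 says that "generalized linear mixed models (GLMMs) [71] will be employed", and describes the model so: "The model will evaluate changes over time (T0, T1, T2) and differences between groups (TRsA, TRcA, CeT), with outcome scores serving as dependent variables". On the right-hand side, "Independent variables (fixed factors) will include time, group, and the interaction term (time × group" are the named terms. Section 2.8 names neither a baseline covariate nor a constraint on the arm means at T0.

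Section 2.1 fixes the order of events: "Following enrollment and the baseline assessment, each participant will be randomly assigned into one of the following three groups". Section 2.6.1 defines the endpoint: "The primary outcome will be the assessment of change (T0-T1-T2) in static and dynamic balance", on the Mini-BESTest.

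Section 2.2 gives the planning values. The effect and spread are "Assuming a minimal clinically important difference (MCID) of 3 points (ds group 1 = 5.75, ds_group 2 = 5.98"; the error rates are "a statistical power of 80% (type I error rate of 0.05"; the result is "an allocation ratio of 1:1:1, 48 subjects per group are required". Section 2.2 does not say whether the two SDs are of scores or of changes, nor whether the test is one-sided or two-sided.

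**The concern.** A group main effect together with a full time × group interaction gives nine free cell means for three arms at three visits. Three of those cells are the arm means at T0. Because T0 is measured before allocation, randomization already tells us that these three share one true value. The model does not use that fact, so it estimates the treatment effect by subtracting the whole observed T0 difference between arms. A baseline-adjusted analysis subtracts only the part of that difference that predicts the follow-up score.

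Precision of the primary contrast is what is at stake. The T0 score is collected on everyone anyway, and the same applies to every secondary outcome measured at T0.

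**Working it through.** **Inputs.** Difference 3 points, SDs 5.75 and 5.98, 48 per group, power 80%, alpha 0.05 (Section 2.2). T0, T1 and T2 as responses with time, group and time × group (Section 2.8). Randomization after T0 (Section 2.1). The correlation rho between T0 and T1 scores is not in the documents; I take 0.5 to 0.9 as an assumed range.

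**Step 1: the plan's own figure.** Pooled SD = √[(5.75² + 5.98²)/2] = 5.866, so d = 3/5.866 = 0.511. For a two-sample t-test:

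- one-sided 5%: n = 48 per group, power 80.0%. This reproduces the stated 48.
- two-sided 5%: n = 61 per group; power at 48 is 69.8%. This does not reproduce it.

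**Step 2: what the written contrast estimates.** With complete data and an identity link, the T1 time × group contrast is (mean T1 − mean T0 in one arm) − (mean T1 − mean T0 in the other). Mixed models fitted to three simulated data sets (three arms of 48, three visits) agreed with this difference in mean change to about 12 decimals.

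**Step 3: variance.** Take a common score SD σ at T0 and T1, and n per arm.

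- Written model: (2/n) × 2σ²(1 − rho)
- Baseline-adjusted: (2/n) × σ²(1 − rho²)
- Ratio, adjusted to written: (1 − rho²) / [2(1 − rho)] = (1 + rho)/2

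Generalized least squares under compound symmetry, with 48 per arm and σ = 5.866, gives the same result:

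| rho | Free T0 means | T0 means constrained equal | Ratio |
|---|---|---|---|
| 0.5 | 1.434 | 1.075 | 0.75 |
| 0.7 | 0.860 | 0.731 | 0.85 |
| 0.8 | 0.574 | 0.516 | 0.90 |

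If 5% of participants have no data after T0, the ratios become 0.759, 0.856 and 0.905, so the planned drop-out hardly matters.

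**Step 4: power, with the stated SDs read as SDs of change.** The written model then has the power of Step 1. Adjustment replaces the SD by 5.866 × √[(1 + rho)/2]; at rho 0.5 that is 5.866 × √0.75 = 5.080. Noncentral t, 94 degrees of freedom, 48 per arm:

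| Assumed rho | Variance saved | n per arm matching 48 unadjusted | One-sided power, from 80.0% to | Two-sided power, from 69.8% to |
|---|---|---|---|---|
| 0.5 | 25% | 36.0 | 89.0% | 81.7% |
| 0.6 | 20% | 38.4 | 87.2% | 79.2% |
| 0.7 | 15% | 40.8 | 85.4% | 76.7% |
| 0.8 | 10% | 43.2 | 83.6% | 74.3% |
| 0.9 | 5% | 45.6 | 81.8% | 72.0% |

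**Step 5: power, with the stated SDs read as SDs of scores.** The SD of change is then 5.866 × √[2(1 − rho)] and the adjusted SD is 5.866 × √(1 − rho²). One-sided power goes from 80.0% to 89.0% at rho 0.5, from 94.1% to 96.7% at 0.7, and from 98.9% to 99.4% at 0.8. The variance saving is the same as in Step 4, but at higher rho there is little power left to gain.

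**Step 6: does dropping the group main effect impose the constraint?** No. The design matrix for time plus the full time × group interaction has rank 9 with or without the group main effect, so it is the same model. Time plus group terms at T1 and T2 only has rank 7 (3 + 2 × 2), which removes the two free T0 differences.

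**The case against.** The strongest reply is that nothing here is invalid. The contrast is unbiased over randomizations, and it matches an endpoint that Section 2.6.1 words as change. That stands: the point is about efficiency. A reader might infer that regression to the mean biases the result. It does so only conditionally, in a sample where the arms happen to differ at T0, and not on average.

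A second reply is that a condensed article leaves covariates and contrasts to an analysis plan that is not shown. This stands for link, covariance structure and further covariates. It does not remove the point, because the article itself puts T0 in the response and names the free group terms. An added covariate list would not change that parameterization.

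Third, a reader might infer from the two-sided figures that the model leaves the trial at 70% power. The documents do not support that. No sidedness is stated, and the 48 per group reproduces only with a one-sided test, where the written model has 80.0%. The gap between 80.0% and 69.8% belongs to the separate question of sidedness. Nor does Section 2.8 say whether the diseases are pooled; with 96 per arm and SDs of change, two-sided power is already 94.1%.

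Fourth, a reader might infer that the plan will report a treatment effect diluted by a third, through a group main effect averaged over T0, T1 and T2. Section 2.8 says that the model is to capture main effects as well as interactions, but it never names the group main effect as the treatment effect. The one-third figure also assumes equal effects at T1 and T2, which the documents do not state. All that remains is a caution against using that term.

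**Conclusion.** The point holds as a free improvement, not as an error that threatens validity. As written, the analysis is a change-score comparison that does not use the equality of T0 means guaranteed by design. Baseline adjustment lowers the variance of the primary contrast by 25%, 20%, 15%, 10% and 5% at rho of 0.5, 0.6, 0.7, 0.8 and 0.9. At the one-sided setting that reproduces 48 per group, and with the SDs read as SDs of change, power rises by 9.0 percentage points at rho 0.5 and by 1.8 at rho 0.9.

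These sizes rest on an assumed rho, equal score variances at T0 and T1, an identity link and little missing data. With another link or intermittent missing data, the equivalence to change scores is approximate. The conclusion that the free-baseline model is less precise does not depend on which rho below 1 is chosen; how much it matters does.

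**What to change.** Amend Section 2.8, or the analysis plan, before unblinding to one of two forms:

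1. Model T1 and T2 as the responses, with the T0 score and T0 × time as covariates, alongside time, group and time × group.
2. Keep T0, T1 and T2 as responses, and constrain the arm means to be equal at T0. Include time, and group × post-baseline time indicators for T1 and T2 only, with no group term at T0. Omitting the group main effect while keeping the full time × group interaction is not enough.

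The two are nearly equivalent for an identity link with little missing data. The second keeps everyone with baseline data in the model directly, which fits the modified intention-to-treat set in Section 2.8.

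State that the arm differences at T1 and at T2 are the treatment effects, and that a group effect averaged over T0 will not be used as one. Apply this to every outcome measured at T0.

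The cost is a few sentences. No extra data, visits or participants are needed.
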